### Study Design

To evaluate the intervention effectiveness, we will conduct a cluster randomized controlled trial (cRCT), where informal settlements are randomized. The clusters include five informal settlements grouped into three sites that are randomized in a 1:1:1 method to one of three study arms. Although outcome data will be collected at the level of the individual, we selected cluster randomization over individual randomization because the intervention is implemented at the settlement level. A cluster randomized design addresses threats of internal validity. It reduces the possibility of experimental contamination due to the shared social and physical environments between youth in the same or nearby informal settlements [35]. Data will be collected at the following three time points: baseline enrollment into the intervention, 8 months after enrollment, and 12 months after enrollment.

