### Outcomes

#### Primary Outcomes

The primary outcomes measured in this trial are as follows:

Changes in HIV testing frequency: This is measured as participants’ self-reported last HIV test. To capture changes, this measure is assessed at all three study time points (baseline [Time 1], 8 months [Time 2], and 12 months [Time 3]).Changes in knowledge of HIV status: To address social desirability bias challenges regarding self-reported HIV serostatus, multiple steps are employed. First, at each timepoint (Time 1, Time 2, and Time 3), participants are asked their current HIV status. At Time 3, participants are offered a completely voluntary rapid HIV test. Knowledge of HIV status will be assessed as correct for persons who agree to take the rapid test and correctly report their HIV status (prior to receiving the result).Changes in linkage to confirmatory HIV testing: Participants in trial arms 1 and 2 (HIV self-testing and mHealth HIV self-testing intervention) are asked at Time 2 and Time 3 if they used their HIV self-testing kit. For those who respond affirmatively, they will be asked the result, and those who report a positive result will be asked if and where they received confirmatory testing.Changes in linkage to HIV care: Participants who seroconvert during the study are asked the frequency of accessing HIV care service since diagnosis. This will be assessed at Time 2 and Time 3.HIV self-testing kit use: To understand the frequency of HIV self-testing kit use and to reduce social desirability bias regarding HIV self-testing kit use, participants in trial arms 1 and 2 will be followed up 1 month after Time 3 to request for purchasing unused kits back. Participants will not be informed of this as an option prior to this time.

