### Sample Size and Power Analysis

Cluster sizes of 130 per group (n=390) are required to have 80% power (*P*<.05) to detect a 25% difference (39% [5] vs 64% tested) in HIV testing between any two groups from three pairwise comparisons (control vs arm 1, control vs arm 2, and arm 1 vs arm 2) for an odds ratio of 1.66. We assume an intraclass correlation coefficient of 0.013 based on HIV research on condom use in sub-Saharan Africa [50]. With 10% attrition, 432 participants (144 per cluster) are required. Computations were performed using RStudio version 3.3.0 (RStudio Team), based on formulae for multiple comparisons of proportions, and adjusted for design effect [51].

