### Data Analysis Plan

Analysis and reporting will be conducted in accordance with CONSORT (Consolidated Standards of Reporting Trials) guidelines [52] (Multimedia Appendix 1). The analyst will be blinded to group allocation. A flow diagram will be used to illustrate patient flow (screening, randomization, allocation, and follow-up). Baseline data will be reported for all three arms and summarized as mean (SD) or median (first quartile, third quartile) for continuous variables and as count and number (percentage) for categorical variables. Primary analysis will involve intention-to-treat analysis (data from participants will be analyzed according to their allocation, irrespective of whether they actually received that intervention). Between-group comparisons will be performed using multilevel mixed effect logistic or linear regression models (to account for clustering), depending on which outcome is being evaluated. For these models, the intervention group will be entered as a fixed effect. The level of significance will be set at α=.05, but adjusted using the Bonferroni method for secondary outcomes [53]. The results will be expressed as odds ratios or mean differences as appropriate, accompanied by 95% CIs and *P* values. We will conduct adjusted analysis for the primary outcome (changes in HIV testing frequency) to investigate the role of various covariates in the relative effect. We will build mixed effect multilevel logistic regression models with the intervention group as the independent variable and HIV testing uptake in the past 3 months (yes/no) as the dependent variable. Covariates (eg, age) will be entered as a block. We will explore gender differences in primary and secondary intervention outcomes.

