### Strengths and Limitations of This Study

The Tushirikiane study is unique in exploring HIV self-testing feasibility and uptake among urban refugee and displaced youth in Kampala, Uganda. Little is known about the preferred HIV testing strategies in this population.

Our three-arm cRCT longitudinal design will allow us to examine changes over time and assess if HIV self-testing alone or HIV self-testing alongside an mHealth component (bidirectional supportive SMS) increases HIV testing uptake and status awareness in comparison with the standard of care.

Our cluster randomization by informal settlements (“slums”) mitigates threats to internal validity and experimental contamination due to the shared social and physical environments between youth in the same or nearby informal settlement.

The primary study limitations are loss to follow-up, missing data points, and study delays due to COVID-19.

Our research will provide gender- and age-stratified analyses, as well as an understanding of the potential added benefits of SMS support strategies alongside HIV self-testing to inform differentiated HIV testing strategies among urban refugee and displaced youth, which can be adapted for diverse contexts.

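### HIV testing and the secondary outcomes are defined as changes, but the stated models name no baseline-outcome or wave term, so stable differences between the three sites could enter the arm effect

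*Protocol article*

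**What the plan says.** All references are to the Protocol article.

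- **Outcome.** Primary Outcomes lists change in HIV testing frequency and says "To capture changes, this measure is assessed at all three study time points". Secondary Outcomes introduces depression and the other measures as changes, and Data Collection and Management places outcome collection at three time points. Strengths and Limitations says that the longitudinal design "will allow us to examine changes over time".
- **Main models.** The Data Analysis Plan specifies multilevel logistic or linear models that account for clustering: "For these models, the intervention group will be entered as a fixed effect". No other fixed effect is named.
- **Adjusted model.** This is given for testing alone. The paragraph again calls the outcome a change, then takes "HIV testing uptake in the past 3 months (yes/no) as the dependent variable", with intervention group as the independent variable. It adds: "Covariates (eg, age) will be entered as a block".
- **Design.** Study Design describes "five informal settlements grouped into three sites that are randomized in a 1:1:1 method", so each arm is one site. Study Setting says that the settlements were chosen purposively.

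**The concern.** A change outcome needs a model that uses the starting value: as a covariate, through a time-by-arm term, or as a change score. The written specification does none of these. It regresses a level on arm and leaves open whether baseline, follow-up or all rows are used.

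In a trial with many clusters this would mostly cost efficiency. Here each arm is a single site, so randomization cannot be relied on to balance prior testing habits or mood scores between arms. The participant's own Time 1 value is the main protection already in hand, and the stated models do not name it.

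**Working it through.** **Inputs.** Rates of 39% and 64% and an ICC of 0.013 (Sample Size and Power Analysis); three waves (Primary Outcomes); one site per arm (Study Design).

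**The plan's own target.** The article plans to "detect a 25% difference (39% [5] vs 64% tested) in HIV testing".
- Difference: 64 − 39 = 25 points.
- Odds ratio: (0.64/0.36) / (0.39/0.61) = 1.778 / 0.639 = 2.78.

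The article states an odds ratio of 1.66, which these rates do not give (the risk ratio is 0.64/0.39 = 1.64). That is a separate matter. I use 2.78 because it follows from the stated rates.

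**Reading A: only follow-up rows enter, with no baseline term.**
- Between-site variance = ICC × p(1 − p) = 0.013 × 0.39 × 0.61 = 0.00309; SD = 0.0556, or 5.6 points.
- Difference between two single-site arms: SD = √(2 × 0.00309) = 0.0786, or 7.9 points.
- 95% range: ±1.96 × 7.9 = about ±15 points.

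This is the chance gap between sites before any intervention. Whatever part of it persists to follow-up is counted as arm effect. With no true effect, control at 39% and an assumed stable gap:

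| Assumed gap | Rates compared | Apparent odds ratio |
|---|---|---|
| 5 points | 44% vs 39% | (0.44/0.56)/(0.39/0.61) = 1.23 |
| 10 points | 49% vs 39% | (0.49/0.51)/(0.39/0.61) = 1.50 |
| 15 points | 54% vs 39% | (0.54/0.46)/(0.39/0.61) = 1.84 |

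**Reading B: all three waves are pooled, with arm as the only term.** Assume 39% in both arms at baseline, 39% in control throughout, and 64% at both follow-ups in the intervention arm.
- Intervention arm average: (0.39 + 0.64 + 0.64)/3 = 0.557; control 0.39.
- Difference: 16.7 points, two thirds of 25.
- Odds ratio: (0.557/0.443)/(0.39/0.61) = 1.96 instead of 2.78.

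Readings A and B are alternatives and do not add up.

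**What a baseline term can do.** A constant site gap cancels in a change contrast. With the participant's own Time 1 value as a covariate, it is removed only as far as that value predicts later responses: on a linear scale with within-person slope b, about (1 − b) × gap remains. For an assumed b of 0.5 and a 10-point gap, that is 5 points. A gap that opens after baseline because one site follows its own trend is removed by neither method, since site and arm coincide.

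**The case against.** The strongest reply is that this is a condensed article. Saying that group is a fixed effect does not say it is the only one. The covariate list is open and could include baseline testing. Wave terms and full covariate lists commonly sit in a SAP, which is not shown. Much of this stands, and it rules out several stronger readings:

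- A reader might infer that the plan excludes baseline adjustment. It does not; for testing it leaves room for it.
- A reader might infer that the effect will be diluted to 16.7 points. Nothing says that baseline rows will be pooled, and the power section, which contrasts 39% with 64%, reads more naturally as a follow-up comparison.
- A reader might extend the point to every primary outcome. Both linkage outcomes are taken only at Time 2 and Time 3, and unused kits are bought back after Time 3. Correct knowledge of status rests on a rapid test offered only at Time 3, and enrolment requires a self-reported negative status, so Time 1 status offers little to adjust for.
- The ICC comes from condom-use research, so the ±15 points show plausible scale and are not an estimate for these sites.

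The reply does not dispose of the point. The article is not silent: it fixes the dependent variable, the independent variable and an example covariate, and together these give a level model for an outcome it calls a change. The covariate block is confined to testing, so it cannot help the secondary outcomes. A change score would serve for the continuous scales, but the article does not say that one will be used.

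**Conclusion.** The point holds for HIV testing and for the secondary outcomes with a Time 1 value. The models as written do not estimate the stated change, and they name no use of the baseline value.

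The size is conditional. In a follow-up comparison, a chance site gap with SD about 7.9 points (95% about ±15) is exposed, resting on the plan's ICC, a 39% rate and one site per arm; only its stable part carries through. If baseline rows were pooled, 25 points would become 16.7, given equal baselines, a flat control arm and the full effect at both follow-ups. That figure is not an expected result.

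A reader might also infer that adding the baseline value makes the arm comparison sound. It does not: with one site per arm, site-specific trends remain confounded with arm under any such model. This is a specification to correct, and correcting it does not cure the design.

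**What to change.** For HIV testing and each secondary outcome with a Time 1 value, state that the Time 2 and Time 3 responses will be modelled with arm, wave, arm-by-wave and the participant's own Time 1 value of the same outcome, with a participant random intercept for the repeated responses. Name in advance the wave that gives the primary contrast; Time 3 is one reasonable choice. Leave out the linkage and kit-use outcomes, which have no Time 1 value.

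Add that this addresses stable site differences only and that site-specific trends remain confounded with arm. A supportive analysis with Time 1 as a response, reading the arm-by-wave terms, would show whether conclusions depend on the form of adjustment. The participant intercept does not settle how clustering by site is handled; that still has to be stated.

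The cost is a few sentences, using data already planned. The Results section places the final wave after publication, so a Time 3 contrast could be fixed before those data exist. For binary outcomes the adjusted odds ratio becomes conditional on the baseline value, a small cost in interpretation; its standard error on the log scale need not fall.

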## Methods

### Study Aim and Objectives

This study aims to evaluate the feasibility and clinical effectiveness of two HIV self-testing delivery approaches (HIV self-testing intervention alone and HIV self-testing combined with a two-way supportive SMS mHealth intervention) in comparison with the standard of care in terms of HIV testing uptake among refugee and displaced youth aged 16 to 24 years in Kampala, Uganda. The specific objectives of this study are to determine the effectiveness of the interventions on the following criteria: (1) increased frequency of HIV testing; (2) increased knowledge of HIV status; (3) increased linkage to confirmatory testing (for those with an HIV positive self-test); and (4) increased linkage to HIV care (for persons testing positive for HIV in HIV self-testing and confirmatory testing). Secondary outcomes include (1) depression, (2) condom use self-efficacy, (3) consistent condom use, (4) sexual relationship power, (5) HIV stigma, and (6) adolescent sexual and reproductive health (SRH) stigma.

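### Bonferroni for the secondary outcomes is valid, but Holm's step-down procedure has the same .05 family-wise bound and never rejects fewer hypotheses: an optional, nearly free improvement

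*Protocol article*

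**What the plan says.** The Data Analysis Plan fixes alpha at .05 and says that it will be "adjusted using the Bonferroni method for secondary outcomes". It does not use the word single-step, but an unqualified Bonferroni method ordinarily means the same alpha/m threshold for every test.

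Six secondary outcomes are listed under Study Aim and Objectives: "Secondary outcomes include (1) depression, (2) condom use self-efficacy, (3) consistent condom use, (4) sexual relationship power", followed by HIV stigma and adolescent sexual and reproductive health stigma.

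The article does not say whether the family is counted by outcome (6 tests) or by outcome and pair of arms (6 × 3 = 18). The sample size section names "three pairwise comparisons (control vs arm 1, control vs arm 2, and arm 1 vs arm 2"), but only for HIV testing.

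On reporting, the Data Analysis Plan says: "The results will be expressed as odds ratios or mean differences as appropriate, accompanied by 95% CIs and *P* values". It does not say whether the intervals for the secondary outcomes are adjusted.

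**The concern.** Bonferroni holds every test to the strictest threshold. Holm uses that threshold only for the smallest P value and relaxes it after each rejection. The family-wise bound stays at .05, with no assumption about correlation between tests. As a pure testing rule, Bonferroni is therefore dominated: any hypothesis it rejects, Holm also rejects, and Holm sometimes rejects more.

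At stake are real effects on outcomes such as depression, stigma or sexual relationship power. Some could be declared non-significant under Bonferroni but significant under Holm, at the same guaranteed error limit. The usual reason to prefer Bonferroni is that it has simple matching simultaneous intervals, and the plan does not visibly use that advantage, because it promises plain 95% CIs.

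**Working it through.** **Inputs.** Alpha .05 and the Bonferroni method come from the Data Analysis Plan, and the six outcomes from Study Aim and Objectives. The family size is 6 or 18, and both are shown. The protocol states no power or effect size for any secondary outcome, so there is no figure of its own to reproduce on this point. Its one computed sample size concerns HIV testing and does not depend on how secondary outcomes are adjusted.

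**Assumptions.** Each true effect is sized for 80% power at unadjusted two-sided .05, that is 1.960 + 0.842 = 2.80 standard errors. The test statistics have common correlation 0.3 unless stated otherwise.

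**Step 1: Bonferroni controls what it should.** With six tests the threshold is .05/6 = .0083. If the tests are independent and all null, family-wise error is 1 − (1 − .0083)^6 = 4.9%. Unadjusted it would be 1 − .95^6 = 26.5%.

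**Step 2: power per true effect under Bonferroni.**
- Six tests: the two-sided critical value at .05/6 is 2.638, so power is Φ(2.802 − 2.638) = 56.5%.
- Eighteen tests: the critical value at .05/18 is 2.991, so power is Φ(2.802 − 2.991) = 42.5%.

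These do not depend on how many effects are real or on the correlation.

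**Step 3: Holm.** Order the P values from smallest to largest. Compare the j-th with .05/(m − j + 1) and stop at the first failure. For six tests the thresholds are .0083, .0100, .0125, .0167, .025 and .05. As an invented illustration, P values of .004, .009, .011, .015, .020 and .040 give one rejection with Bonferroni and six with Holm.

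**Step 4: average power per true effect, by simulation (100,000 to 200,000 replicates per scenario).**

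| Tests | True effects | Bonferroni | Holm |
|---|---|---|---|
| 6 | 1 | 56.5% | 56.6% |
| 6 | 2 | 56.5% | 57.9% |
| 6 | 3 | 56.5% | 59.4% |
| 6 | 4 | 56.5% | 61.4% |
| 6 | 6 | 56.5% | 67.3% |
| 18 | 3 | 42.5% | 43.1% |
| 18 | 6 | 42.4% | 44.1% |
| 18 | 12 | 42.4% | 47.0% |

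Holm rejected everything Bonferroni rejected in every replicate. The chance of at least one rejection was identical in every scenario, because both methods apply the same threshold to the smallest P value (for example 86% for both with three of six true). With three of six true, the two methods gave the same set of rejections in about 90% of replicates.

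**Step 5: error actually spent.** With six tests, the chance of any false rejection (Bonferroni vs Holm) is 2.4% vs 3.7% with three true effects and 1.6% vs about 3.1% with four. Both stay below 5%.

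**Step 6: sensitivity.**
- Correlation shrinks the gain. With all six true it is 11.8 points at correlation 0, 10.9 at 0.3 and 9.1 at 0.8.
- If each effect is only 1 standard error, the gain is 0.1 to 0.5 points with two to six true.

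**The case against.** The strongest reply is that the plan contains no error here. It prespecifies a valid, conservative method that achieves its stated control, nothing in the article contradicts it, and no stated figure changes. All of that stands. A reader might infer from Holm's dominance that Bonferroni is wrong; it is not. What remains is that the plan names a particular method for which an alternative with the same guarantee and at least as many rejections exists.

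A reader might also infer that Bonferroni gives up power for nothing. The documents do not support that, for three reasons.
- Bonferroni has direct simultaneous intervals (100 − 5/6 = 99.17% for six tests) and Holm has none as simple. The article leaves open whether its 95% CIs are adjusted, so this benefit is available but not clearly used.
- Holm gains power by spending error room that Bonferroni leaves unused, as step 5 shows. Only the bound is equal.
- Bonferroni also limits the expected number of false rejections to .05. Holm does not (0.040 vs 0.056 for six tests with one true effect at correlation 0.8).

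A further tempting reading is that the secondary scales will move together and so make the gain large. The article gives no basis for expecting most of them to respond: its directional objectives concern the primary outcomes. The gain comes from the number of true effects, and correlation reduces it. The most striking contrast, a chance of detecting all six effects of 12% with Bonferroni and 36% with Holm, needs all six to be real and each to have 80% unadjusted power.

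Finally, the article cites a source for its Bonferroni method, and an analysis plan may exist; neither is at hand. The exact procedure could be spelled out there, though the single-step reading is the natural one.

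**Conclusion.** The point holds as an optional efficiency improvement, not as an error. Under the stated assumptions, Holm adds about 0 points of power per true effect when one of six secondary effects is real, 3 when three are, and 11 when all six are. In an 18-test family it adds under 1 point with three real and about 5 with twelve. These sizes rest on assumed effects, because the protocol gives none. That Holm shares the .05 bound and never rejects fewer hypotheses does not depend on those assumptions.

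The choice of method does not touch a larger issue. The Study Design section randomizes three sites to three arms, so arm and site are confounded. At the protocol's intraclass correlation of 0.013 and 130 per arm, the design effect is 1 + 129 × 0.013 = 2.677. An analysis that ignored clustering would have a true two-sided error of 2 × [1 − Φ(1.96/√2.677)], about 23% per nominal .05 test. Neither Bonferroni nor Holm would then deliver its nominal family-wise error, and Holm should not be presented as a remedy.

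**What to change.** In the Data Analysis Plan, replace the reference to the Bonferroni method with the Holm step-down procedure at family-wise alpha .05. Apply it to the same family the sponsor already intends, and report Holm-adjusted P values beside unadjusted 95% CIs. State that those intervals are unadjusted, since they will not always agree with the Holm decisions.

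If the sponsor intends Bonferroni-adjusted simultaneous intervals, the plan should say so and keep Bonferroni; that is a sufficient reason.

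The cost is one sentence and one standard P-value adjustment option in software, with no change to data collection or sample size. The loss is the simple matching intervals. The change is legitimate only before unblinding. The article, published in February 2021, describes a blinded analyst and a final wave planned for February to March 2021, so at publication it could still be made without knowledge of the results.
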